### Statistical analyses

#### Primary statistical aim

The confirmatory part of the statistical analysis is the assessment of treatment efficacy by testing the null hypothesis (H0), “The survival of patients treated with norfloxacin is equal to the survival of patients treated with placebo”, against the alternative hypothesis (H1), “The survival of patients treated with norfloxacin is better than the survival of patients treated with placebo”, by using a one-sided log-rank test with a significance level α = 5%. Antibiotic primary and secondary SBP prophylaxis with norfloxacin showed no negative effects on survival in previous trials and meta-analyses [7,10,12,13,22]. Moreover, there is no evidence for a preponderance of deleterious treatment effects associated with norfloxacin in this patient group, which justifies a one-sided test. All patients who receive at least one dose of norfloxacin or placebo are included in the analysis as an intention-to-treat approach. Incomplete information is accounted for by censoring.

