## Methods/Design

### Trial design and ethical considerations

The trial has been designed to assess the effect of antibiotic primary prophylaxis on survival in carriers of *NOD2* risk variants without SBP. Figure 1 summarizes the design of the study. The I*N*CA trial is a double-blind, placebo-controlled clinical trial with two parallel treatment arms. It is planned to randomly allocate 186 eligible patients to one of these arms (1:1 ratio). Balanced randomization, stratified for the protein content of the ascites (<15 g/L or ≥15 g/L, given that a low protein content is an established risk factor for SBP) and the study center, will be performed as centralized, computer-based block randomization using separate randomization lists for each stratum. Only the central and independent pharmacy (Heidelberg University Hospital) performing the randomization procedure, and neither the investigators nor the patients, will be aware of the allocation sequence or the block size used. Blinding of participants and study personnel responsible for treatment and outcome assessment is ensured by identical encapsulation of placebo and active substance that makes both indistinguishable, as well as by the use of identical blisters and folding boxes. The unique patient randomization number labeled on the boxes makes the medication patient-specific. The confidential block size ensures randomization concealment after emergency un-blinding because of safety reasons or after unblinding due to SBP. Access to emergency envelopes is regulated at all sites.

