### Frequency and scope of study visits and interventions

All patients who have already developed ascites should be screened for trial participation. Particularly, SBP has to be excluded, and ascitic protein content has to be determined by a clinically indicated index paracentesis (maximally 10 days prior to baseline visit). Patients who cannot undergo paracentesis because of small amounts of ascites can be included in the trial only if SBP is unlikely, taking into account clinical and blood test indicators. Hereafter potentially eligible patients must be informed about the study and genetic testing by an investigator with the use of a specific information sheet. Informed consent to study participation and genetic testing is mandatory for a further evaluation of patients, and especially *NOD2* genetic testing, using patients’ blood specimens. At the baseline visit (within 28 days before randomization) and during treatment within the trial, only noninvasive or minimally invasive interventions are scheduled (Table 3). Patients who fulfill all inclusion criteria but no exclusion criteria proceed to randomization. Treatment with the study medication must be initiated within 7 days after randomization. Adverse reactions to the study medication are more likely to occur early after treatment initiation, so that closely scheduled visits are implemented for the first 4 weeks. Thereafter, and for the remainder of the trial, the study visits are less frequent (Table 4) and, at predefined time points only, telephone interviews are scheduled to record any (serious) adverse event (AE) as well as primary and secondary endpoint information. Patients are regularly treated within the trial for 12 months. Patients who must definitely stop the study medication for any reason (for example, SBP,prolongation of QTc above 500ms [QTc; QT interval corrected for heart frequency using Bazett’s formula]) will complete the trial without taking the trial medication and attend the regular visits. Patients with SBP during the trial will be unblinded. Patients who undergo liver transplantation or who revoke their consent to participate are censored for the analysis with the date of withdrawal.

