**Table 3 Tab3:** **Study-specific actions**
^**a**^

**Action**	**Baseline period**	**Study visits**	**Telephone visits**
Informed consent	X		
Checking inclusion and exclusion criteria	X		
Demographics	X		
Medical history (with focus on liver disease)	X		
*NOD2* genetic testing	X		
Concomitant diseases	X	X	X
Concomitant medications	X	X	X
MELD and Child-Pugh-scores	X	X	
Clinical assessment and vital signs	X	X	
12-lead ECG	X	X	
Blood tests (safety parameters)	X	X	
Recording of adverse events		X	X
Distribution and return of study medication		X	
Collection of ascites samples (clinically indicated puncture)	X	X	
Collection of stool samples		X	

^a^ECG, Electrocardiography; MELD, Model For End-Stage Liver Disease.

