#### Secondary statistical aims

As an exploratory analysis, and in order to identify further predictor variables for survival, a multivariate Cox regression method is used. It incorporates baseline variables and the occurrence of infectious complications that require antibiotics as time-dependent variables. Tests are two-sided with a significance level of α = 5%. To avoid overfitting, we apply the rule of thumb and include at most enough independent variables that ten or more events per independent variable are still observed.

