#### Sample size calculation

To identify a difference of 20% survival rate after 12 months (60% versus 40%, one-sided log-rank test, α = 0.05, 1 − β = 0.8), and to account for a 17% loss due to dropout during treatment, 186 patients carrying *NOD2* variants have to be included in the trial. Sample size calculation is based on the previous observation that patients carrying at least one *NOD2* variant have a deleterious outcome with a survival of only 40% within 12 months, as compared to 73% of patients with wild-type genotypes at all three *NOD2* loci [18], and an increase in survival rate from 48% to 60% after 12 months in a recent randomized controlled trial in which SBP primary prophylaxis was investigated without taking *NOD2* genotypes into account [17]. In studies in which norfloxacin was administered for 12 months or longer to patients with liver cirrhosis and ascites, non-compliance rates ranged from 5% to 8% [17,23]. Although loss to follow-up has been inconsistently reported, the two landmark studies on secondary SBP prophylaxis had rates of up to 9% for loss to follow-up. As a conservative estimate, we calculated our projected sample size with the reported maximum of 17% loss to follow-up and non-compliance. Among all patients considered for the I*N*CA trial, only 25% carry at least one *NOD2* risk allele [18]. Moreover, we expect that 25% of eligible patients to drop out because of lack of informed consent, and a maximum of 10% of the total number of patients with ascites are expected to present with SBP, leading to exclusion. Thus, a total of 1,380 patients with cirrhosis and ascites initially need to be evaluated for the study. Patients evaluated but not included are documented and reported according to the CONSORT statement (http://www.consort-statement.org/).

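### The primary log-rank test, as described, does not use the ascitic-protein stratum or baseline MELD: it is valid and adequately powered, but some efficiency is forgone (minor)

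*Protocol article*

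**What the plan says.** - **Primary test.** Under 'Primary statistical aim', survival is compared "by using a one-sided log-rank test with a significance level α = 5" percent. 'Sample size calculation' rests on the same test ("one-sided log-rank test, α = 0.05"). Neither section mentions strata or covariates.
- **Randomisation.** 'Trial design and ethical considerations' stratifies by ascitic protein at two levels, below 15 g/L and 15 g/L or above, "given that a low protein content is an established risk factor for SBP". It also stratifies by study center, with a separate list for each stratum. 'Participants' foresees at least 13 centers.
- **Baseline severity.** Table 3 lists "MELD and Child-Pugh-scores" in the baseline period.
- **Multivariable model.** 'Secondary statistical aims' describes an exploratory Cox model meant to find predictors of survival: "It incorporates baseline variables and the occurrence of infectious complications that require antibiotics as time-dependent variables".
- **Protein value.** 'Frequency and scope of study visits and interventions' requires ascitic protein from the index paracentesis. It then adds: "Patients who cannot undergo paracentesis because of small amounts of ascites can be included in the trial only if SBP is unlikely". Table 1 makes the same allowance.

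**The concern.** If randomisation is balanced on a factor that predicts the outcome and the test ignores that factor, the usual log-rank variance is somewhat too large. The test then rejects less often than its nominal level under the null and loses some power under the alternative. Baseline MELD raises a related question: a strong predictor of death would sharpen the treatment comparison, but the primary test does not use it.

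Two smaller matters bear on any remedy. Patients enrolled without paracentesis have no obvious place in a two-level protein stratum. And the one multivariable model described conditions on infections during treatment, which lie on the route by which norfloxacin is expected to act, so it is not a suitable source for an adjusted treatment effect. At stake is efficiency in a trial of 186 patients that needs about 1,380 to be evaluated.

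**Working it through.** **1. Reproduce the planned size.** Inputs from 'Sample size calculation': 12-month survival 60% versus 40%, one-sided α 0.05, power 0.80, and 17% loss.

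- Hazard ratio: ln 0.6 / ln 0.4 = 0.5575.
- Freedman events: ((1 + 0.5575)/(1 − 0.5575))² × (1.645 + 0.842)² = 12.39 × 6.18 = 76.6, so 77.
- Evaluable patients: 77 / 0.5 = 154, where 0.5 is the mean of the death proportions 0.6 and 0.4.
- With loss: 154 / 0.83 = 185.5, so 186.

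The stated figure reproduces exactly for the plain log-rank test, so the planned 80% power already belongs to that test.

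**2. Assumptions for the comparison.** The article does not say how strongly protein, MELD or center predicts death, so these are varied: protein hazard ratio 1 to 3 with half the patients in each level, MELD hazard ratio 1 to 2 per SD, and center log-hazard SD 0 to 0.3. There are 154 evaluable patients, censored at 12 months. Overall survival is held at 60% versus 40% throughout, as in the plan.

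**3. Size of the plain test (one-sided, nominal 5%).**

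| Protein hazard ratio for death | Plain test |
|---|---|
| 1.5 | 4.6% |
| 2 | 4.4% |
| 3 | 3.7% |

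The protein-stratified test is at about 5.0%. A second simulation, with blocks of four within protein by 13 centers and 25,000 runs per cell, gave 4.9% at 1.5 and 4.0% at 3 for the plain test. Its stratified and adjusted tests were at 4.8 to 5.3%. The simulation standard error there is √(0.05 × 0.95 / 25,000) = 0.14 points. The direction agrees, and the departure from 5% is small unless protein is strongly prognostic.

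**4. Power (second simulation, 4,000 runs per cell).**

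| Assumed prognostic effects | Plain | Stratified by protein | Stratified by protein × center | Stratified by protein, MELD-adjusted |
|---|---|---|---|---|
| None | 80.8% | 80.5% | 77.0% | 80.2% |
| Protein 1.5 | 82.2% | 82.6% | 78.9% | 82.4% |
| Protein 2 | 82.2% | 83.8% | 80.5% | 83.8% |
| Protein 3 | 84.0% | 88.2% | 84.8% | 88.2% |
| Protein 1.5, MELD 1.5, center SD 0.2 | 81.8% | 82.4% | 79.4% | 86.0% |
| Protein 1.5, MELD 2, center SD 0.2 | 83.4% | 83.5% | 80.7% | 90.9% |
| Protein 2, MELD 2, center SD 0.3 | 83.0% | 84.1% | 81.4% | 91.6% |

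Differences from the plain test:

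- **Protein alone:** −0.3, +0.4 and +1.6 points at hazard ratios 1, 1.5 and 2, and +4.2 at 3.
- **Protein with MELD adjustment:** +4.2, +7.5 and +8.6 points in the three MELD rows, and −0.6 when nothing is prognostic.
- **Protein by center:** between −1.6 and −3.8 points in six of the seven rows, and +0.8 at protein hazard ratio 3.

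The loss with center comes from sparse strata: 13 centers × 2 levels = 26 strata, so 154 / 26 ≈ 6 patients and 77 / 26 ≈ 3 deaths in each.

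**The case against.** The strongest objection is that the article never says 'unstratified'. It is a condensed account, and a full protocol or analysis plan may already name strata. This stands as a limit on the point: it concerns the test as described. The suggestion still holds, because analysing by a factor already used in randomisation is a specific, better method.

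Stronger readings are tempting, but the article does not support them:

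- **The test is invalid or underpowered.** It is neither. Size is at or below 5%, and the plain test keeps 81 to 84% power in every scenario. Lower figures arise if 0.5575 is fixed as the hazard ratio within strata and only placebo survival is set to 40%. Norfloxacin survival is then 59.3% or 58.2% at protein hazard ratios of 2 and 3, and 56.1% with a strong MELD effect added, which is less than the planned 60%.
- **Protein is an established predictor of death.** The article calls low protein a risk factor for SBP. A link to death is plausible, because the Background ties infection to mortality, but no figure is given.
- **Leaving out MELD makes the test conservative.** MELD is not a randomisation factor. Omitting it forgoes power but does not shrink the size by this mechanism.
- **The exploratory Cox model will supply the treatment effect.** The article describes it as a search for predictors and claims no treatment effect from it.
- **Stratification is free.** Stratifying by both randomisation factors usually loses power, so the gain depends on leaving center out.

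**Conclusion.** The point holds as a minor efficiency improvement, not as an error. The plain one-sided log-rank test controls the type I error and meets the stated 80% power. If protein predicts death, the test is conservative by about 0.4, 0.6 and 1.3 percentage points at hazard ratios of 1.5, 2 and 3 (5.0 minus 4.6, 4.4 and 3.7). It then forgoes about 0 to 2 points of power up to a ratio of 2 and about 4 points at 3. Using MELD as well brings the gain over the plain test to about 4 to 9 points for a MELD hazard ratio of 1.5 to 2 per SD, at a cost of about 1 point if nothing is prognostic.

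All of these sizes rest on assumed prognostic strengths and equal protein strata. Only the direction follows from the design. Separately, the two-level randomisation stratum and the admission of patients without paracentesis need to be reconciled.

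**What to change.** - **Primary test.** State before unblinding that the log-rank test is stratified by ascitic protein: below 15 g/L, 15 g/L or above, and 'not measured' for patients enrolled without paracentesis. Do not stratify the test by center.
- **Patients without a protein value.** Reconcile 'Trial design and ethical considerations' with 'Frequency and scope of study visits and interventions', so that it is clear how these patients are assigned to a randomisation list.
- **Supportive estimate.** Report the treatment hazard ratio from a Cox model stratified by protein in the same way and adjusted for baseline MELD.
- **Exploratory model.** Add a sentence that no treatment effect is read from the Cox model with time-dependent infections.

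The cost is a change of analysis wording. Sample size, visits and data collection stay as they are. If protein and MELD turn out not to be prognostic, the loss is at most about 1 point of power, and that falls on the MELD-adjusted analysis.

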#### Secondary statistical aims

As an exploratory analysis, and in order to identify further predictor variables for survival, a multivariate Cox regression method is used. It incorporates baseline variables and the occurrence of infectious complications that require antibiotics as time-dependent variables. Tests are two-sided with a significance level of α = 5%. To avoid overfitting, we apply the rule of thumb and include at most enough independent variables that ten or more events per independent variable are still observed.

#### Safety

Safety parameters are assessed by competing risk analysis. In addition, descriptive statistics on safety parameters are added, using two-sided tests at a significance level of 5%.

#### Sample size calculation

To identify a difference of 20% survival rate after 12 months (60% versus 40%, one-sided log-rank test, α = 0.05, 1 − β = 0.8), and to account for a 17% loss due to dropout during treatment, 186 patients carrying *NOD2* variants have to be included in the trial. Sample size calculation is based on the previous observation that patients carrying at least one *NOD2* variant have a deleterious outcome with a survival of only 40% within 12 months, as compared to 73% of patients with wild-type genotypes at all three *NOD2* loci [18], and an increase in survival rate from 48% to 60% after 12 months in a recent randomized controlled trial in which SBP primary prophylaxis was investigated without taking *NOD2* genotypes into account [17]. In studies in which norfloxacin was administered for 12 months or longer to patients with liver cirrhosis and ascites, non-compliance rates ranged from 5% to 8% [17,23]. Although loss to follow-up has been inconsistently reported, the two landmark studies on secondary SBP prophylaxis had rates of up to 9% for loss to follow-up. As a conservative estimate, we calculated our projected sample size with the reported maximum of 17% loss to follow-up and non-compliance. Among all patients considered for the I*N*CA trial, only 25% carry at least one *NOD2* risk allele [18]. Moreover, we expect that 25% of eligible patients to drop out because of lack of informed consent, and a maximum of 10% of the total number of patients with ascites are expected to present with SBP, leading to exclusion. Thus, a total of 1,380 patients with cirrhosis and ascites initially need to be evaluated for the study. Patients evaluated but not included are documented and reported according to the CONSORT statement (http://www.consort-statement.org/).

## Discussion

The impaired intestinal mucosal barrier with subsequent bacterial translocation is considered to represent one of the key pathophysiological mechanisms leading to SBP in patients with cirrhosis [24,25]. In 2001, variants of the *NOD2* gene were associated with impaired mucosal barrier function in Crohn’s disease [26]. Because *NOD2* is involved in the intestinal recognition of bacteria, insufficient activation of nuclear factor κB and recruitment of autophagy-related proteins in carriers of *NOD2* risk variants might result in deficient destruction of bacteria and promote their translocation from the intestine [27]. In line with this, the *NOD2* germline variants p.R702W, p.G908R and c.3020insC were found to be predictors of the development of infectious complications and mortality in patients with cirrhosis [18,19]. It has also been reported that the *NOD2* variants are associated with reduced survival in sepsis [28].

In 2007, a randomized controlled trial in which a clinically defined high-risk group of patients with cirrhosis and ascites was investigated showed that primary prophylaxis with norfloxacin improved the 3-month probability of survival (94% versus 63%; *P* =0.03) [17]. However, according to a recent Cochrane review [14], all previous studies (538 patients) on primary SBP prophylaxis were underpowered to assess survival over a 12-month period. Thus, further trials are needed to substantiate prevention strategies. Because broad-spectrum antibiotic prophylaxis might be hampered by the selection of resistant bacteria [29], long-term antibiotics should be administered only to the subgroups with the highest risk, which has yet to be defined [10,30].

The I*N*CA trial thus evaluates the effect of antibiotic primary prophylaxis on survival in a genetically defined high-risk group. Because no gold standard for the management of patients with cirrhosis with ascites, but without SBP, has been established and current consensus guidelines [10] have not implemented general recommendations for antibiotic primary prophylaxis in these patients, randomization to placebo and surveillance of patients with wild-type *NOD2* is admissible and ethical. Data suggesting beneficial effects of antibiotic prophylaxis in patients with cirrhosis with low ascitic protein content (<15 g/L) is limited, and survival analyses are conflicting [14]. Hence, until more reliable data are available, randomization to placebo for these patients has been considered ethical. In cases of obvious disadvantages for the patients in the low ascitic protein content stratum treated with placebo, the DSMB will propose appropriate measures so that there are no uncontrolled risks for participating patients.

Norfloxacin, a poorly absorbed antibiotic with activity predominantly against Gram-negative bacteria, has been widely studied in patients with liver cirrhosis and is documented to be safe in these patients. Alternative drugs include ciprofloxacin or co-trimoxazole, but evidence for SBP prophylaxis is not as robust as that of norfloxacin [10]. The fully non-absorbable antibiotic rifaximin represents a promising alternative, but it has not yet been assessed in randomized controlled trials for prevention of SBP [31-33]. The norfloxacin dose of 400 mg per day is chosen because it was used successfully in previous studies for the primary prophylaxis of SBP in patients with low ascitic protein content [17,23], and this is the standard dose for secondary prophylaxis of SBP [10,30].

The primary endpoint of the I*N*CA trial is the overall survival over a period of 12 months. This endpoint has been chosen to assess the benefit of the intervention for patients in relation to current average waiting times for liver transplantation [34]. The occurrence of SBP has been selected as a secondary endpoint because the hypothesis underlying antibiotic prophylaxis refers to the impaired mucosal barrier in the intestine causing intra-abdominal infections such as SBP [24,25]. In case of SBP during study participation, microbiological analyses may help to calculate the frequency of quinolone-resistant SBP. Although it has been shown that these infections respond to the recommended antibiotics in most cases [14], they may confer a specific risk for patients receiving norfloxacin. Specimens taken during the study (ascites, stool) may enable us to clarify whether a potentially increased frequency of infections with resistant bacteria is due to intestinal selection or selective translocation of quinolone-resistant bacteria or whether it is associated with specific changes or “enterotypes” of the intestinal microbiome [35,36]. The occurrence of any clinically significant infection other than SBP has been chosen as a secondary endpoint because the spread of bacteria across the intestinal mucosal barrier could promote other infectious complications also influencing the patients’ outcome. An excess of infections requiring antibiotic treatment in one of the treatment arms provides information on whether antibiotic prophylaxis promotes or avoids potentially life-threatening infections at other sites. Finally, the secondary endpoint of hospitalization allows us to assess health care costs and quality of life.

For safety reasons, special attention is paid to the occurrence of AEs throughout the I*N*CA trial. Owing to the high *a priori* risk of trial participants, we expect a large number of AEs and serious AEs. Moreover, we predict a mortality of up to 60% in our cohort. To avoid excess mortality in one of the study arms, the progress of the I*N*CA trial is supervised by a DSMB.

Individualized diagnosis and treatment approaches are key themes for future research directives and may substantially change health care for individual patients. Up to 50% of patients awaiting liver transplantation die as a result of infectious complications [37]. Although preventive strategies are required to avoid life-threatening infections in these patients, a broad and unselected use of antibiotics can also trigger resistant bacteria and worsen outcome. Thus, a better selection of patients and personalized approaches that direct interventions only to patients with the highest risk are urgently needed [30]. The I*N*CA trial meets this need by suggesting stratified prevention based on risk assessment. The I*N*CA trial is the first in the field of hepatology with an aim to rapidly transfer and validate information on individual genetic risk into clinical decision algorithms.

